# Nurse Practitioner–Led Integrated Rapid Access to HIV Prevention for People Who Inject Drugs (iRaPID): Protocol for a Pilot Randomized Controlled Trial

**DOI:** 10.2196/42585

**Published:** 2022-10-11

**Keywords:** HIV prevention, people who inject drugs, sexual risk, pre-exposure prophylaxis, opioid agonist therapy, medications for opioid use disorder, opioid use disorder

## Abstract

**Background:**

The ongoing volatile opioid epidemic remains a significant public health concern, alongside continued outbreaks of HIV and hepatitis C virus among people who inject drugs. The limited access to and scale-up of medications for opioid use disorder (MOUD) among people who inject drugs, coupled with multilevel barriers to pre-exposure prophylaxis (PrEP) uptake, makes it imperative to integrate evidence-based risk reduction and HIV prevention strategies in innovative ways. To address this need, we developed an integrated rapid access to HIV prevention program for people who inject drugs (iRaPID) that incorporates same-day PrEP and MOUD for this population.

**Objective:**

The primary objective of this pilot study is to assess the feasibility and acceptability of the program and evaluate its preliminary efficacy on PrEP and MOUD uptake for a future randomized controlled trial (RCT). We also aim to explore information on the implementation of the program in a real-world setting using a type I hybrid implementation trial design.

**Methods:**

Using a type I hybrid implementation trial design, we are pilot testing the nurse practitioner–led iRaPID program while exploring information on its implementation in a real-world setting. Specifically, we will assess the feasibility and acceptability of the iRaPID program and evaluate its preliminary efficacy on PrEP and MOUD uptake in a pilot RCT. The enrolled 50 people who inject drugs will be randomized (1:1) to either iRaPID or treatment as usual (TAU). Behavioral assessments will occur at baseline, and at 1, 3, and 6 months. Additionally, we will conduct a process evaluation of the delivery and implementation of the iRaPID program to collect information for future implementation.

**Results:**

Recruitment began in July 2021 and was completed in August 2022. Data collection is planned through February 2023. The Institutional Review Boards at Yale University and the University of Connecticut approved this study (2000028740).

**Conclusions:**

This prospective pilot study will test a nurse practitioner–led, integrated HIV prevention program that incorporates same-day PrEP and MOUD for people who inject drugs. This low-threshold protocol delivers integrated prevention via one-stop shopping under the direction of nurse practitioners. iRaPID seeks to overcome barriers to delayed PrEP and MOUD initiation, which is crucial for people who inject drugs who have had minimal access to evidence-based prevention.

**Trial Registration:**

ClinicalTrials.gov NCT04531670; https://clinicaltrials.gov/ct2/show/NCT04531670

**International Registered Report Identifier (IRRID):**

DERR1-10.2196/42585

## Introduction

With opioid use disorder being intricately linked to HIV transmission via drug injection, the United States is witnessing resurgent twin opioid and HIV epidemics, fueled by concurrent rises in opioid-related overdoses [1-6]. People who inject drugs remain disproportionately affected by HIV [7] despite their engagement in preventable drug- and sex-related risk behaviors [8-14]. There is an urgent need to combine evidence-based harm reduction services and HIV prevention strategies in innovative ways to effectively curb HIV incidence.

Critical elements in the HIV prevention toolbox for people who inject drugs include medication for opioid use disorder (MOUD), syringe services programs (SSPs), pre-exposure prophylaxis (PrEP), and HIV treatment as prevention. MOUD minimizes the risk of fatal overdose and effectively reduces HIV transmission by decreasing or eliminating the frequency of injection [15-21], while SSPs narrow transmission risk with each protected injection [22,23]. Nevertheless, access to these programs among people who inject drugs is often limited, with overall coverage remaining low [24-27] despite data documenting increased HIV incidence in people who inject drugs where MOUD and SSPs are unavailable [28-30]. HIV treatment as prevention requires active case-finding and effective linkage to HIV treatment, which is markedly improved when people with HIV gain access to MOUD [31].

PrEP is an essential additional tool for people who inject drugs [32,33]. It is not restricted to specially licensed prescribers and reduces HIV transmission from not only drug injection but also sex. Although integrating PrEP into existing evidence-based risk reduction programs can strengthen HIV prevention efforts for people who inject drugs [16,17,19-21,34], its scale-up has been hampered for several reasons. First, PrEP and MOUD each require a separate prescription. They are often delivered in different settings and by clinicians with varying areas of expertise [35], generating excess demands on patients and making access to care more difficult for people who inject drugs. Furthermore, the provision of PrEP and MOUD prescriptions is unnecessarily complex. The traditional PrEP delivery model requires multiple visits before the prescription. Existing data show high attrition rates between initial screening and PrEP initiation, adding to the attrition observed between PrEP referral and initiation [36,37]. The prescription of MOUD also has its own set of demands [38], some of which are regulated by the Drug Enforcement Agency. PrEP and MOUD have been mainly prescribed in a “centralized” care delivery model that focuses more on physicians, is costly, and limits accessibility. There also remains a suboptimal supply of prescribers [39-41], with many physicians reluctant to prescribe medications to people who inject drugs [42-45].

An innovative approach of coprescribing PrEP and MOUD on the same day can streamline delivery, as it addresses impediments to PrEP and MOUD uptake. Same-day PrEP prescription is a safe, feasible, and acceptable approach to linking at-risk individuals to much-needed PrEP care early on [46-48] while decreasing attrition rates between the initial visit and prescription time and increasing adherence [49]. This approach also sets the stage to boost PrEP uptake and makes the current standard of care, which already comprises streamlined access to and initiation of MOUD, more inclusive. The provision of same-day MOUD, when integrated with PrEP, provides the added benefit of stabilizing patients and can therefore strongly complement and facilitate PrEP initiation, adherence, and persistence as has been observed with antiretroviral therapy [34,50]. Additionally, it has the potential to overcome provider-level barriers, increasing the confidence that patients will maintain their treatment regimen [43,45].

With ongoing calls for task shifting to support the expansion of HIV prevention services [51], there is a need to “decentralize” PrEP delivery by incorporating it into front-line prevention services provided by nurse practitioners (NPs). Nurse-led PrEP delivery is a viable strategy that can lead to rapid increases in PrEP service capacity without additional resources [39,52]. Furthermore, the 2016 Comprehensive Addiction and Recovery Act permits NPs to prescribe buprenorphine with waivers, paving the way for PrEP and MOUD coprescription. This decentralized delivery model represents an innovative approach to scale-up integrated HIV prevention services among people who inject drugs.

We developed an NP-led, integrated rapid access to HIV prevention program for people who inject drugs (iRaPID) that incorporates same-day access to PrEP and MOUD. The primary objective of this pilot study is to assess the feasibility and acceptability of the program and evaluate its preliminary efficacy on PrEP and MOUD uptake for a future randomized controlled trial (RCT). We also aim to explore information on the implementation of the program in a real-world setting using a type I hybrid implementation trial design.

## Methods

### Study Design

The protocol involves a type I hybrid implementation trial design [53], where we pilot test the NP-led iRaPID program. The study is a 2-arm RCT that examines the feasibility and acceptability of the program among people who inject drugs and clinical stakeholders. In the process, we can provide a preliminary estimate of the efficacy of PrEP and MOUD uptake by comparing the iRaPID program against treatment as usual (TAU) among HIV-negative people who inject drugs. We hypothesize that the iRaPID program will be more efficacious than will TAU on PrEP and MOUD uptake and adherence.

In this type I hybrid implementation trial design, we collect process measures to inform future implementation efforts. We will explore potential patient- and provider-level barriers and facilitators of the program regarding its implementation in real-world settings. More specifically, we will assess at both these levels the overall satisfaction, perceived utility, and relevance of each intervention component; determine the relevant needs of the target population (ie, people who inject drugs), thereby delineating intervention characteristics that address those needs; and explore the barriers to implementation of the iRaPID program, such as logistical barriers and time and resource constraints. Finally, changes needed to accommodate same-day coprescription of PrEP and MOUD will be established, along with the resources and structural changes necessary for the successful implementation of the program.

### Ethics Approval

The institutional review board at Yale University approved this protocol (#2000028740) with an institutional reliance agreement with the University of Connecticut. This study is registered at ClinicalTrials.gov (NCT04531670).

### Study Setting

This study is being conducted at the New Haven Syringe Service Program (NHSSP) in Connecticut, the first SSP in the United States (established 1986). With steadily high-ranking and rising fatal and nonfatal accidental overdose rates over the past few years, New Haven continues to bear the detrimental impacts of a severe opioid crisis and reflects the nationwide picture of a twin opioid and HIV epidemic, with a high HIV prevalence among people who inject drugs in the city [54,55]. The NHSSP offers services beyond New Haven to exurban and rural communities and integrated medical services through the Community Health Care Van, a 40-foot mobile medical clinic, and minivans that provide personalized services [56-60].

### Study Procedures

#### Recruitment and Screening

Recruitment for the trial started in July 2021 at the NHSSP and lasted until August 31, 2022. People who inject drugs were recruited on-site through posted flyers at the central and mobile distribution locations of the NHSSP, word of mouth, and community-based outreach. Individuals are screened initially by phone or in person to assess whether they meet the eligibility criteria, which include being 18 years or older; having a confirmed HIV-negative status; self-reported injection drug use in the past 6 months; OUD based on *The Diagnostic and Statistical Manual of Mental Disorders, Fifth Edition* criteria; and substantial ongoing HIV risk factors (eg, condomless sex, needle sharing) in the past 6 months. Uninsured participants were referred to an on-site case manager for assistance with insurance enrollment.

#### Informed Consent, Enrollment, and Randomization

After confirming eligibility criteria and providing informed consent, all participants underwent a baseline assessment, which took approximately 90 minutes and was administered electronically by a trained research staff member in a private room at NHSSP. Participants were then randomized (1:1) to receive either the iRaPID intervention or TAU. Randomization was done via REDCap software (Vanderbilt University), a secure, HIPAA (Health Insurance Portability and Accountability Act)-compliant web app with a built-in randomization feature that allows the development of a defined randomization model. Randomization was stratified by sex to ensure that an equal proportion of participants is present in both arms. Participants are assessed at baseline, and 1-, 3-, and 6-month time points. This approach allows us to examine short-term outcomes and the decay and emergence of intervention effects. Study participants are reimbursed for the time required to complete the assessments (US $35 for the baseline assessment and US $25 for each follow-up assessment).

### Intervention Procedures

#### Treatment as Usual

Participants randomized to the TAU group will follow the existing clinical guidelines to receive PrEP, MOUD, or both medications. They are provided with a comprehensive list of PrEP and MOUD programs available in the area. Since PrEP and MOUD services are not integrated within the current standard of care, participants will have to be screened at separate visits (one for PrEP and another for MOUD) if they are interested in both programs unless they find a prescriber who will provide both.

For PrEP, the current standard of care generally involves 2 clinical appointments. During the first visit, patients are assessed for eligibility and PrEP readiness and receive additional counseling on using PrEP. Additionally, laboratory screenings are ordered. During the second visit, which usually occurs 1 to 3 weeks later, the laboratory results are reviewed, PrEP readiness is reassessed, and the patient is provided with a PrEP prescription that they will need to fill at a pharmacy. Access to MOUD also entails 2 separate clinic visits at least 3 days apart. The first encompasses an eligibility assessment, patient counseling, and an evaluation of the patient's readiness to start therapy. Patients are also given a home induction kit and asked to follow up in 3 days for further counseling on maintenance therapy (Figure 1).

**Figure 1 figure1:**
[figure not shown]
Integrated care process for same-day PrEP and MOUD compared to TAU. iRaPID: integrated rapid access to HIV prevention program for people who inject drugs; MOUD: medication for opioid use disorder; PrEP: pre-exposure prophylaxis; TAU: treatment as usual. *Patients interested in methadone prescriptions are referred to a methadone (or other appropriate) addiction treatment center.

#### iRaPID Intervention

The iRaPID program was developed by adapting TAU services for PrEP and MOUD to accommodate same-day coprescription for both medications through a single nurse provider. We used the modified participatory, evidence-based, patient-focused process for advanced practice nursing [61] to guide the optimal use of the NP-led model and refined it to incorporate the same-day coprescription of PrEP and MOUD. Participants randomized to the iRaPID group will receive a prescription for PrEP and MOUD and educational counseling by an NP, followed by safety checks via phone calls or SMS text messages on days 5 and 10; and a clinical visit on day 30 (Figure 1).

During the first day, the NP evaluates the participant's eligibility for PrEP and assesses PrEP readiness. Participants eligible for PrEP are evaluated using the Centers for Disease Control and Prevention's PrEP clinical practice guidelines [62], including acute HIV infection symptoms and laboratory testing for HIV, hepatitis (ie, hepatitis A, B, and C viruses), creatinine, pregnancy (for females), and sexually transmitted infections (ie, gonorrhea, chlamydia, and syphilis). During the same visit, they will also be offered a PrEP prescription for a 30-day supply.

Additionally, the NP assesses MOUD readiness. Participants are screened for buprenorphine maintenance therapy (BMT) eligibility according to the Drug Addiction Treatment Act of 2000 and Treatment Improvement Protocol Series 43 criteria [63]. As methadone maintenance therapy (MMT) is only provided in specialty settings, only BMT is offered at the study site (NHSSP). Patients preferring MMT over BMT are referred to initiate same-day MMT. If the participant is eligible for BMT, a drug toxicology screen is performed, and participants are provided with office or home induction and resources to assist them in self-managing their opioid treatment [64]. The resources provided include a home induction kit with an instruction sheet, BMT film packets, nonsteroidal anti-inflammatory drugs (for body pain), hydroxyzine (for anxiety and insomnia), and loperamide (for diarrhea). Additionally, patients receive adherence and potential medical adverse events counseling.

After the laboratory results become available (typically within 3 days following the visit), the NP contacts the participant (on day 5) via a phone call or SMS text message to review the test results and inquire about MOUD stabilization. If test results are concerning and warrant PrEP discontinuation (which is typically rare) [65-68], participants are urged to cease PrEP immediately. On day 10, the NP contacts the participant using the same modality to inquire about PrEP adherence, possible side effects, and MOUD dosing as well as to troubleshoot potential billing issues. On day 30, the NP prescribes a 60-day supply of PrEP and a 30-day supply of MOUD and provides counseling related to long-term maintenance of PrEP and MOUD. In the case of a positive test result for any disease or laboratory value outside the normal range, participants are referred to appropriate clinical care according to the standard of care at any time point during the study. The study’s timeline and activities are summarized in Table 1.

**Table 1 table1:** Study activity and measures.

Study activity			Timeline													
			Screening (prebaseline)		Evaluation (baseline)		Treatment					Retention				
							Day 5		Day 10		1 month			3 months		6 months
Eligibility assessment			✓													
Informed consent					✓											
**TAU^a^ PrEP^b^**																
	PrEP educational counseling^c^			✓									✓		✓	
	Lab screenings			✓									✓		✓	
	Lab result review^c^			✓									✓		✓	
	PrEP prescription^c^			✓									✓		✓	
**TAU MOUD^d^**																
	Office/home induction			✓												
	Buprenorphine kit			✓												
	Follow-up appointment							✓					✓		✓	
**iRaPID^e^**																
	Educational counseling^f^			✓				✓								
	PrEP prescription			✓						✓			✓		✓	
	Safety check					✓		✓								
	Day 30 check-up			✓												
	Follow-up appointment							✓					✓		✓	
Research interview					✓									✓		✓
DBS^g^											✓			✓		✓
Qualitative interview														✓		✓
Payment					✓						✓			✓		✓

^a^ TAU: treatment as usual.

^b^PrEP: pre-exposure prophylaxis.

^c^Exact day depends on when the laboratory results are available for the clinician (usually 3-7 days after baseline assessment).

^d^MOUD: medication for opioid use disorder.

^e^iRaPID: integrated rapid access to HIV prevention program for people who inject drugs.

^f^PrEP and MOUD educational counseling.

^g^DBS: dried blood spot.

### Strategies To Maximize Recruitment and Retention

Based on our previous research experience [69-72], we are using several strategies to maximize recruitment and minimize attrition rates. Our recruitment strategies include community-based outreach (eg, through flyers and public advertisements), cross-organizational collaborations, and referrals from harm reduction services such as SSPs and mobile clinics. Moreover, the research team routinely meets with the community-based stakeholders (eg, clinical team members, counselors at the MMP, and staff at the SSPs) to ensure proper screening of participants and the smooth function and operation of all study components.

Strategies to promote retention include rapid enrollment, thorough explanation of study requirements, integration of the research program within community-based clinical and nonclinical settings (eg, SSPs, mobile clinics, addiction treatment centers), close monitoring of participants' clinical status, and accessibility of study staff to patients for questions and problems. Participant locator forms, which include name, address, phone number, and family or friend contact, are collected and updated at each visit. Members of the research staff call or message each participant (according to their previously stated preferred contact method) 1 week and 1 day before the date of their visit. We also issue appointment cards at each visit for subsequent ones. Furthermore, participants are compensated based on the time and effort required to complete the assessments based on the market rate, which has also been an essential retention strategy.

### Outcome Measures

The study will assess the feasibility, acceptability, and preliminary efficacy of the iRaPID intervention using a range of instruments administered at various time points throughout the study. The feasibility and acceptability of the program will be evaluated using both quantitative (in-depth interview) and qualitative (one-to-one interview) mechanisms. Data collected include the following: a quantitative assessment of process indicators, standardized acceptability measures collected through quantitative interviews, and measures of fidelity gauged through implementation checklists. Feasibility will be assessed by quantitative process indicators collected by the research staff, including the number of participants screened, recruited, randomized, retained, and adherent to treatment. Acceptability of the intervention will include a 10-item acceptability rating profile and an intervention fidelity assessment. The acceptability profile [73] will be collected through in-depth quantitative interviews at each follow-up point. We will also examine participants' views on acceptability, areas of perceived usefulness of the program, and their confidence in starting PrEP and MOUD. Ultimately, intervention fidelity will be collected using an implementation checklist specific for each part of the program (ie, baseline visit, safety check, follow-up, and clinical visit on day 30), which NPs will complete, documenting the activities covered in each program domain.

We will also estimate the preliminary efficacy of PrEP and MOUD uptake in this pilot RCT of the iRaPID intervention versus TAU (primary outcome). This will be determined by assessing PrEP and MOUD uptake (ie, current use). For those who initiate PrEP, we will also evaluate the time to PrEP initiation, along with adherence and persistence on PrEP, as part of the secondary outcome. Time to PrEP initiation will be calculated by recording the number of days between the first encounter with the NP or health care provider and the day of initiation of PrEP, validated by the pharmacy PrEP pick-up date. We will measure PrEP adherence using the visual analog scale [74] and confirm with dried blood spot testing [75-77]. Persistence on PrEP will be measured by assessing pharmacy data, including both refill (if refilled within 30 days after exhausting PrEP from previous fill or not) and pick-up information. Given the importance of moderating factors on the effect of efficacy, we will measure individual (eg, sociodemographic, sexually transmitted infection, drug use, depression), social (eg, social support), and structural (eg, stigma, physician distrust) factors at each in-depth interview.

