### Statistical Analyses

Feasibility will be assessed through the analysis of data collected by the research team, including the number of participants screened and enrolled per month, the proportion of eligible participants who enroll in the study, the treatment-specific proportion of participants completing follow-up visits, rates of adherence to the intervention protocol, and fidelity of implementation measured by the percentage of domains captured by the NPs at each time point. Acceptability analysis will be based on descriptive statistics from the acceptability measures, such as simple means and percentages between treatment arms, and thematic analysis of qualitative data collected in postimplementation focus groups.

Meanwhile, preliminary efficacy analysis will assess the hypothesis that the iRaPID intervention will perform better than TAU over time using a primary outcome (ie, PrEP uptake) and secondary outcomes (ie, time to PrEP initiation, PrEP adherence and persistence). We will first test baseline characteristics for homogeneity between treatment arms using an independent-samples *t* test or Wilcoxon rank sum test (if unequal variances are assessed) for continuous variables and chi-square tests or Fisher exact tests (if any small cell sizes) for categorical variables. This analysis of baseline characteristics will be used to determine significantly different factors to include in the final model for adjustment. To assess our hypotheses relating to preliminary efficacy, we will use a generalized linear mixed model [78] with random subject effects to account for the correlation in repeated measurements that occur within subjects. Treatment assignment, time, and the interaction between time and treatment assignment, including confounders such as sociodemographic characteristics and prior PrEP or MOUD engagement, will be included as covariates. The proportion of participants that initiate PrEP will be estimated and compared using the linear contrast statement in SAS PROC GLIMMIX (SAS Institute). Similar analyses will be conducted for other outcomes, including MOUD uptake, time to PrEP initiation, optimal adherence to PrEP, and PrEP persistence.

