### Limitations and Setbacks

The pilot trial has several limitations. Our study is restricted to 1 geographical location (Greater New Haven area, CT), potentially limiting the generalizability of our findings to all people who inject drugs across different geographic settings, particularly areas with fewer or absent SSPs. Further, the prescribing privileges of NPs have geographical disparities of their own, as they only have fully independent practice authority in 29 US commonwealths, states, and territories [81], which undermines nationwide program implementation in areas with physician shortages. Additionally, the study relies on self-reported measures of prior drug use, HIV-related risk behaviors, sexual behaviors, and some measures of primary outcomes (eg, adherence to PrEP using the visual analog scale). Impression management might occur to heighten protocol eligibility, which could potentially lead to the overreporting of risk behaviors during screening and subsequent discrepancies between data collected at different time points. Participants in the pilot trial include both out-of-treatment and in-treatment people who inject drugs (ie, those who were on BMT or MMT at the time of enrollment), which can affect treatment and adherence outcomes, especially as participants who were already on BMT or MMT at the time of enrollment did not undergo induction as compared to their out-of-treatment counterparts.

We also encountered many setbacks regarding participant recruitment due to the COVID-19 pandemic and the recurrent surge of cases in the area. Due to the nature of our program mandating in-person laboratory tests and assessments, ensuing research laboratory closures, and programmatic policies and changes that were developed to ensure research staff safety at the workplace (such as shift schedule changes and remote work) negatively affected recruitment efforts.

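### MOUD uptake is scored as current use although people already on buprenorphine or methadone were enrolled, so the comparison mixes new starts with continued treatment

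*Protocol article*

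**What the plan says.** Outcome Measures makes MOUD uptake part of the efficacy question: "We will also estimate the preliminary efficacy of PrEP and MOUD uptake in this pilot RCT of the iRaPID intervention versus TAU (primary outcome". It then gives the scoring rule: "This will be determined by assessing PrEP and MOUD uptake (ie, current use".

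Limitations and Setbacks describes who was enrolled: "Participants in the pilot trial include both out-of-treatment and in-treatment people who inject drugs", the latter being "those who were on BMT or MMT at the time of enrollment". It adds that "participants who were already on BMT or MMT at the time of enrollment did not undergo induction", and it accepts that the mix can influence outcomes, but it does not change the outcome definition.

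The criteria listed under Recruitment and Screening include opioid use disorder and "self-reported injection drug use in the past 6 months". None of them concerns current MOUD.

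Statistical Analyses plans a generalized linear mixed model with arm, time and their interaction, "including confounders such as sociodemographic characteristics and prior PrEP or MOUD engagement, will be included as covariates". There the named primary outcome is PrEP uptake alone, and MOUD comes later: "Similar analyses will be conducted for other outcomes, including MOUD uptake". Randomization was stratified by sex.

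Nothing in the article limits the MOUD uptake analysis to people off MOUD at enrollment, and nothing redefines uptake as initiation.

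**The concern.** A person on buprenorphine or methadone at randomization meets the definition of uptake at every visit while they remain in that treatment, whichever arm they are in. They have taken nothing up. The measured proportion in each arm is therefore a blend of two quantities: new starts among people off MOUD, and retention among people already on it.

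The introduction and discussion present the program as a way past barriers to starting treatment, so new starts are what the MOUD comparison should estimate. The pilot is also meant to inform a future trial. Blended rates would mislead its planning in two ways. Each arm's uptake rate would be too high if retention exceeds new uptake, and the difference between arms would not be the uptake effect.

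**Working it through.** The article gives no in-treatment share, uptake rate or retention rate, and its sample-size statement gives no error rate, power or numeric effect. There is no figure of the plan's own to reproduce on this point. Everything below except the 50 participants and 1:1 allocation (Abstract) is an assumption. I take 25 per arm.

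**Formula.** Let f be the share on MOUD at enrollment (equal in both arms), p the rate of new uptake among the rest, and r the share of in-treatment participants still on MOUD at the visit.

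- Measured rate in an arm = f·r + (1 − f)·p
- Measured difference = (1 − f)·(p_iRaPID − p_TAU) + f·(r_iRaPID − r_TAU)

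**Equal retention.** The second term vanishes, so the difference shrinks by the factor (1 − f), whatever r is. With p = 50% versus 20% (30 points) and r = 90%:

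| f | iRaPID | TAU | Difference |
|---|---|---|---|
| 10% | 0.09 + 0.45 = 54% | 0.09 + 0.18 = 27% | 27 points |
| 20% | 0.18 + 0.40 = 58% | 0.18 + 0.16 = 34% | 24 points |
| 40% | 0.36 + 0.30 = 66% | 0.36 + 0.12 = 48% | 18 points |
| 60% | 0.54 + 0.20 = 74% | 0.54 + 0.08 = 62% | 12 points |

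**Unequal retention.** Take f = 40% and the same new uptake.

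- Retention 90% versus 70%: 66% versus 0.28 + 0.12 = 40%, a difference of 26 points, of which 18 come from uptake and 8 from retention.
- Retention 90% versus 60%: 66% versus 0.24 + 0.12 = 36%, a difference of 30 points. It equals the uptake effect only by coincidence (18 + 12).

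**Covariate adjustment.** I fitted a single-visit logistic model to expected cell counts at f = 40%, with equal retention and a main effect for MOUD status at enrollment. The true odds ratio among people off MOUD is 4.0.

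| Retention | Unadjusted OR | Adjusted OR |
|---|---|---|
| 85% | 2.09 | 2.70 |
| 90% | 2.10 | 2.96 |
| 98% | 2.14 | 3.70 |

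Adjustment recovers part of the odds ratio. It does not restore the difference in proportions.

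**Chance imbalance.** If 20 of 50 were in treatment, the hypergeometric probability that the arms differ by at least 20 points in that share is 0.148 (with an even total this means 6 or more people).

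**Cost of restricting the analysis.** At f = 40%, 15 per arm remain.

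- 95% half-width, restricted: 1.96·√[(0.25 + 0.16)/15] = 32 points.
- 95% half-width, all participants at 66% versus 48%: 1.96·√[(0.2244 + 0.2496)/25] = 27 points.
- Power (two-sided 5%, no dropout, full and equal retention): restricted 51%, 40% and 28% at f = 20%, 40% and 60%; all participants scored as current use 39%, 25% and 16%.

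On these assumptions the interval is wider, but power is not lost, because the effect is no longer diluted.

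**The case against.** The strongest reply has four parts.

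- **The plan already adjusts.** Earlier MOUD engagement is a named covariate, and baseline factors that differ significantly are added to the model. A reader might infer that stratifying by sex alone leaves imbalance in MOUD status uncorrected. The article does not support that, because the covariate largely answers it. What remains is that a main effect leaves continued use counted as uptake, and that earlier engagement is not clearly the same as being on MOUD at enrollment.
- **Dilution is not certain.** A reader might infer that the difference must shrink towards zero. That requires similar retention in both arms. The iRaPID schedule includes a day-30 MOUD prescription and counselling about staying on treatment, and the authors hypothesize better adherence, so retention could differ by arm. This objection stands, and the working shows both cases.
- **Current use in everyone is a legitimate quantity.** It estimates the proportion on MOUD and keeps all 50 participants. That is fair, and it is a reason to keep it as a supplementary summary. It does not measure uptake.
- **The detail may sit in the full protocol or analysis plan.** Subgroup handling could. But the article itself states the definition and itself reports the enrollment of people in treatment, so the point rests on what is written.

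**Conclusion.** The point holds, with its size left conditional. As written, the rule scores continuation of treatment begun before randomization as uptake. This raises an arm's rate whenever retention among in-treatment participants exceeds new uptake in that arm. With similar retention in both arms, the difference in proportions falls by the in-treatment share. From an assumed 30 points, that is a loss of 3 points if one in ten was in treatment and 18 points if six in ten were. With unequal retention, the direction of the distortion is not determined and the result cannot be read as an uptake effect.

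Two limits apply. The article is inconsistent about whether MOUD uptake is primary: Outcome Measures includes it, while Statistical Analyses names only PrEP uptake. This affects how much the problem matters, not whether it exists. A reader might also extend the concern to PrEP, since both outcomes share the wording on current use. Nothing in the article says that anyone was on PrEP at enrollment, so the PrEP primary outcome is not shown to be affected.

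**What to change.** Make these changes in the analysis plan:

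- Define MOUD uptake as starting MOUD after randomization, and analyse it among participants not on buprenorphine or methadone maintenance at enrollment. This subgroup is fixed before randomization, so the arms remain comparable by design.
- Report continued MOUD use by arm, separately, for those in treatment at enrollment.
- State the number on MOUD at enrollment in each arm.
- Keep current use among all 50 as a supplementary summary, labelled as such.

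The cost is a change of wording. No new data should be needed, because the limitations section shows that treatment status at enrollment was known. The downside is a smaller denominator and possibly a wider interval for MOUD uptake.
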